### **10.1.4 Pregnancy reporting**

#### **Pregnancies**

If a female trial participant becomes pregnant, the trial participant must be asked to read and sign pregnancy consent form to allow the Study Doctor ask about her pregnancy. To ensure participant safety, each pregnancy occurring after signing the informed consent must be reported to Vaxess or designee within 24 hours of learning of its occurrence. The pregnancy should be followed up to determine outcome, including spontaneous or voluntary termination, details of the birth, and the presence or absence of any birth defects, congenital abnormalities, or maternal and/or newborn complications.

Pregnancy should be recorded and reported by the investigator to Vaxess or appropriate designee. Pregnancy follow-up should be recorded on the same form and should include an assessment of the possible relationship to the any pregnancy outcome. Any SAE experienced during pregnancy must be reported.

Pregnancy outcomes should be collected for the female partners of any males who took study treatment in this study. Consent to report information regarding these pregnancy outcomes should be obtained from the mother. Pregnancies should be followed up until birth.

### **10.1.5 Reporting of study treatment errors including misuse/abuse**

Medication errors are unintentional errors in the prescribing, dispensing, administration or monitoring of a medicine while under the control of a healthcare professional, participant or consumer

Misuse refers to situations where the medicinal product is intentionally and inappropriately used not in accordance with the protocol.

Abuse corresponds to the persistent or sporadic, intentional excessive use of a medicinal product, which is accompanied by harmful physical or psychological effects.

Study treatment errors and uses outside of what is foreseen in the protocol will be recorded on the appropriate eCRF irrespective of whether or not associated with an AE/SAE and reported to Safety only if associated with an SAE. Misuse or abuse will be collected and reported in the safety database irrespective of it being associated with an AE/SAE within 24 hours of investigator's awareness.

**Table 8: Guidance for capturing the study treatment errors including misuse/abuse**

| Treatment error type                | Document in Dosing eCRF (Yes/No) | Document in AE eCRF           | Complete SAE form                      |
|-------------------------------------|----------------------------------|-------------------------------|----------------------------------------|
| Unintentional study treatment error | Yes                              | Only if associated with an AE | Only if associated with an SAE         |
| Misuse/Abuse                        | Yes                              | Yes                           | Yes, even if not associated with a SAE |

For more information on AE and SAE definition and reporting requirements, please see the respective sections.

## 10.2 Additional Safety Monitoring

| SERUM                                                | Mild: Grade 1 | Moderate: Grade 2 | Severe: Grade 3 | Potentially Life Threatening: Grade 4 |
|------------------------------------------------------|---------------|-------------------|-----------------|---------------------------------------|
| ALT, AST (liver function tests) increase by a factor | 1.1-2.5 x ULN | 2.6-5.0 x ULN     | 5.1-10 x ULN    | >10 x ULN                             |
| Cr mg/dL                                             | 1.5-1.7       | 1.8-2.0           | 2.1-2.5         | >2.5                                  |
| Blood Urea Nitrogen- BUN mg/dL                       | 23-26         | 27-31             | >31             | Dialysis                              |

- The laboratory values serve as a guide and are dependent on the institutional reference ranges.

## 11 DATA COLLECTION AND DATABASE MANAGEMENT

### 11.1 Data collection

All data should be recorded, handled, and stored in a way that allows its accurate reporting, interpretation, and verification.

Designated investigator staff will enter the data required by the protocol into the eCRFs. The eCRFs have been built using fully validated secure web enabled software that conforms to 21 CFR Part 11 requirements, Investigator site staff will not be given access to the EDC system until they have been trained. Automatic validation programs check for data discrepancies in the eCRFs, allow modification and/or verification of the entered data by the investigator staff.

The investigator/designee is responsible for assuring that the data (recorded on eCRFs) (entered into eCRF) is complete, accurate, and that entry and updates are performed in a timely manner. The Investigator must certify that the data entered are complete and accurate.

After final database lock, the investigator will receive copies of the participant data for archiving at the investigational site.

All data should be recorded, handled, and stored in a way that allows its accurate reporting, interpretation, and verification.

### **11.2 Database management and quality control**

Vaxess personnel (or designated CRO) will review the data entered by investigational staff for completeness and accuracy. Electronic data queries stating the nature of the problem and requesting clarification will be created for discrepancies and missing values and sent to the investigational site as Data Clarification Forms (DCFs) via email. Designated investigator site staff are required to respond promptly to queries and to make any necessary changes to the data.

Concomitant treatments and prior medications entered into the database will be coded using the WHO Drug Reference List, which employs the Anatomical Therapeutic Chemical classification system. Medical history/current medical conditions and adverse events will be coded using the MedDRA terminology.

At the conclusion of a non-IRT study, the occurrence of any emergency code breaks will be determined after return of all code break reports and unused supplies to Vaxess or designate.

Once all the necessary actions have been completed and the database has been declared to be complete and accurate, it will be locked, and the treatment codes will be unblinded and made available for data analysis/moved to restricted area to be accessed by independent programmer and statistician. Any changes to the database after that time can only be made after written agreement by Vaxess development management.

### **11.3 Site monitoring**

Before study initiation, at a site initiation visit, a Vaxess delegated Contract Research Organization (CRO) representative will review the protocol and data capture requirements (i.e. eCRFs) with the investigators and their staff. During the study, Vaxess or designate employs several methods of ensuring protocol and GCP compliance and the quality/integrity of the sites' data. The field monitor will visit the site to check the completeness of participant records, the accuracy of data capture / data entry, the adherence to the protocol and to GCP, the progress of enrollment, and to ensure that study treatment is being stored, dispensed, and accounted for according to specifications. Key study personnel must be available to assist the field monitor during these visits. Continuous remote monitoring of each site's data may be performed by a centralized Vaxess/delegated CRO/Clinical Research Associate (CRA) organization. Additionally, a central analytics organization may analyze data and identify risks and trends for site operational parameters and provide reports to Vaxess clinical team to assist with trial oversight.

The investigator must maintain source documents for each participant in the study, consisting of case and visit notes (hospital or clinic medical records) containing demographic and medical information, laboratory data, electrocardiograms, and the results of any other tests or assessments. All information on eCRFs must be traceable to these source documents in the participant's file. Data not requiring a separate written record will be defined before study start

and will be recorded directly on the eCRFs. The investigator must also keep the original ICF signed by the participant (a signed copy is given to the participant).

The investigator must give the monitor access to all relevant source documents to confirm their consistency with the data capture and/or data entry. Vaxess or designate's monitoring standards require full verification for the presence of informed consent, adherence to the inclusion/exclusion criteria, documentation of SAEs, and of data that will be used for all primary variables. Additional checks of the consistency of the source data with the eCRFs are performed according to the study-specific monitoring plan. No information in source documents about the identity of the participants will be disclosed.

## **12 DATA ANALYSIS AND STATISTICAL METHODS**

Any data analysis carried out independently by the investigator should be submitted to Vaxess before publication or presentation.

### **12.1 Analysis sets**

For all analysis sets, participants will be analyzed according to the study treatment(s) received.

The safety analysis set will include all participants who received any study treatment.

The immunogenicity analysis set will include all participants with at least one available valid (i.e. not flagged for exclusion) immunogenicity concentration measurement, who received any study drug and with no protocol deviations that impact immunogenicity data.

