|-----------------------------------|-------------------------------------------------------------------------------------------------------------------------------------------------------------------------------------------------------------------------------------------------------------------------------------------------------------------------------------------------------------------------------------------------------------------------------------------|-------------------------------|
|                                   | Clinic visit on Days 2 (+1), 4 (+1), 8 ( $\pm 2$ ), 15 ( $\pm 2$ ), 29 ( $\pm 2$ ), 57 ( $\pm 2$ ), 85 ( $\pm 7$ ), 119 ( $\pm 7$ ) and 180 ( $\pm 7$ ) will assess adverse events, concomitant medications, and clinical labs.                                                                                                                                                                                                           |                               |
| IMMUNOGENICITY ASSESSMENTS | Serum hemagglutination-inhibition (HAI) titers will be assessed on pre-vaccination on Day 1, and on Days 29 ( $\pm 2$ ), 57 ( $\pm 2$ ), 85 ( $\pm 7$ ), 119 ( $\pm 7$ ) and 180 ( $\pm 7$ ) after vaccination. Anti-HA, virus microneutralization titers, anti-silk fibroin Immunoglobulin G (IgG) and total IgE titers will be assessed on pre-vaccination on Day 1, and on Days 29 ( $\pm 2$ ), and 180 ( $\pm 7$ ) after vaccination. |                               |
| HALTING RULES              | Event                                                                                                                                                                                                                                                                                                                                                                                                                              | Number of Participants |
|                                   | Death or any life-threatening serious AE (SAE)                                                                                                                                                                                                                                                                                                                                                                                            | 1                             |

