| 
 
To assess the immunogenicity of VX-103 delivered in a single MIMIX MAP dose regimen in healthy adults in <math>\geq 18</math>-39 years of age.
 
To assess VX-103 MIMIX MAP delivery as a dose sparing skin immunization strategy by comparing the safety, reactogenicity, tolerability and immunogenicity of a fractional H1 vaccine dose level (7.5 <math>\mu\text{g}</math>) delivered by MIMIX MAP to a standard H1 vaccine dose level (15 <math>\mu\text{g}</math>) delivered by MIMIX MAP.
 
 |  | 
 
Influenza A H1 geometric mean HAI titer; mean fold rise and seroconversion rates for each treatment group and timepoint on Days 1, 29, 57, 85, 119, 180.
 
MIMIX MAP dose level comparisons in vital signs, laboratory parameters of hematology, clinical chemistry, urinalysis, adverse events, and local and systemic solicited and unsolicited reactogenicity event(s)
 
Influenza A H1 geometric mean HAI titer; mean fold rise and seroconversion rates for each route and timepoint for the fractional dose versus full dose delivered by MIMIX
 
 |  |
| Exploratory objective(s)                                                                                                                                                                                                                                                                                                                                                                                                                                                                                                                                  |  | Endpoint(s) for exploratory objective(s)                                                                                                                                                                                                                                                                                                                                                                                                                                                                                                                                                                              |  |

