## 5.2 Exclusion Criteria

1. Any medical condition that in the judgement of the investigator would make the subject participation in the study unsafe.
2. Any condition, including confirmed or suspected immunosuppressive or immunodeficient condition, that in the judgement of the investigator would make it unsafe for the subject to participate.

3. History of or current autoimmune disease or impaired immune responsiveness (of any cause).
4. Having cancer or received treatment for cancer within three years (persons with a history of cancer who are disease-free without treatment for three years or more are eligible), excluding basal cell carcinoma (BCC) or squamous cell carcinoma (SCC), which are allowed unless located at the vaccination site.
5. Impaired immune responsiveness (of any cause), including diabetes mellitus.
6. Presently receiving or having a recent history of receiving (within the past six months) any medication or therapeutic modality that affects the immune system such as allergy shots, immune globulin, interferon, immunomodulators, radiation therapy, cytotoxic drugs or drugs known to be frequently associated with significant major organ toxicity, or systemic corticosteroids (oral or injectable). Inhaled and topical corticosteroids are allowed.
7. Receipt or plan to receive a non-study vaccine within 30 days prior to VX-103-01 vaccination or 60 days after vaccination.
8. Receipt of any influenza vaccine in previous 24 months and/or planned receipt of influenza vaccine through the duration of the study.
9. Diagnoses influenza infection in the previous 24 months prior to screening.
10. Diagnosed COVID infection via medical personnel or at home test within the past 60 days prior to screening.
11. Female participant who is pregnant or breastfeeding.
12. A tattoo, scar or excessive hair in volar forearm region which would impede assessment of MAP application site.
13. Allergy to influenza vaccine or components, or history of severe local or systemic reaction to any vaccination.
14. History of anaphylactic type reaction to injected vaccines
15. History of or current allergy to latex.
16. History of Guillain-Barré Syndrome.
17. Receipt of any investigational product or nonregistered drug within 30 days prior to vaccination or currently enrolled in any investigational drug study or intends to enroll in such a study within the study period.

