#### 9.1.2 Withdrawal of informed consent

Participants may voluntarily withdraw consent to participate in the study for any reason at any time. WOC occurs only when a participant:

- Does not want to participate in the study anymore,  
and
- Does not want any further visits or assessments  
and
- Does not want any further study related contacts

In this situation, the investigator should make a reasonable effort (e.g. telephone, e-mail, letter) to understand the primary reason for the participant's decision to withdraw his/her consent and record this information.

Where consent to the use of personal and coded data is not required, participant therefore cannot withdraw consent. They still retain the right to object to the further use of personal data.

No further assessments will be conducted, and the data that would have been collected at subsequent visits will be considered missing.

Further attempts to contact the participant are not allowed unless safety findings require communicating or follow-up.

All efforts should be made to complete the assessments prior to study discontinuation. A final evaluation at the time of the participant's study discontinuation should be made as detailed in the assessment schedule (Table 5).

Vaxess or designate will continue to retain and use all research results (data) that have already been collected for the study evaluation.

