### 12.5.3 Immunogenicity

Although clinical efficacy trials of new influenza vaccines may be performed in late-stage development or post-licensure, FDA licensure can be achieved based upon antigen specific HAI titers. The primary immunogenicity analyses will assess HAI GMTs, GMT mean fold rise, seroconversion rates (defined as a fourfold rise in HAI titers) and seroprotection status (defined as an HAI titer of  $\geq 1:40$ ), by HAI.

HAI antibodies in serum will be determined at specific time points for all participants, including the placebo group and all immunogenicity results will be listed by treatment group, ethnicity, participant and visit/time. Summary statistics may be provided as appropriate in case of high incidence of positive participants/samples.

Sera analyzed for determination of HAI titers will be evaluated as follows:

- Calculation of the geometric mean of pre- and post-vaccination HAI titers for each treatment group.
- Change from pre- to post-vaccination in geometric mean HAI titers for each treatment group.
- Seroconversion rate defined as percentage of participants with either a pre-vaccination HAI titer  $< 1:10$  and post vaccination HAI titer of  $\geq 1:40$  or a pre-vaccination HAI titer of  $\geq 1:10$  and a minimum four-fold rise in post vaccination HAI antibody titer at each timepoint.
- Seroprotection rate defined as the percentage of participants with a HAI titer  $\geq 1:40$  at each timepoint for the vaccine H1 strain

Incidence of positive participants and correlation with selected AEs and clinical outcomes may be explored as appropriate in case of high incidence.

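### Section 12.1 excludes the whole participant for a deviation affecting immunogenicity data, with no time limit, so valid titers taken before a late deviation can be lost

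*Protocol*

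**What the plan says.** Protocol section 12.1 sets three conditions for the immunogenicity set. The first admits "all participants with at least one available valid (i.e. not flagged for exclusion) immunogenicity concentration measurement". The other two restrict it to those "who received any study drug and with no protocol deviations that impact immunogenicity data". The sentence therefore contains two exclusion routes. One flags individual measurements as invalid. The other excludes participants because of a deviation. The section does not say when each route applies, and the second has no time limit.

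Table 1 places the secondary HAI endpoints at each "timepoint on Days 1, 29, 57, 85, 119, 180". The synopsis confirms that the first of these is pre-dose: "Serum hemagglutination-inhibition (HAI) titers will be assessed on pre-vaccination on Day 1".

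Section 12.5.3 lists HAI GMT, change in GMT, seroconversion and seroprotection. Its seroconversion definition begins "Seroconversion rate defined as percentage of participants with either a pre-vaccination HAI titer" and needs both a pre-dose and a post-dose titer. Seroprotection needs only a titer at the visit. Section 12.7 plans an interim analysis once all participants have passed Day 57 or left the study.

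**The concern.** Follow-up runs to Day 180, and a participant can give several sound titers before anything goes wrong. Take a non-study influenza vaccine given between Day 85 and Day 119. It could affect the Day 119 and Day 180 titers. It cannot affect those from Days 1, 29, 57 and 85. Because section 12.1 makes freedom from deviations a condition of membership, the participant leaves the set and all six titers go.

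Two things are at stake. The first is precision: the HAI results by arm and visit support the secondary dose-sparing comparison of 7.5 µg with 15 µg, and there are only 15 participants per arm. The second is consistency. Section 12.7 does not list the interim endpoints, but if HAI is among them, the same Day 29 and Day 57 results could be reported on one set of people at the interim and a smaller one at the end, because of events after both visits.

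**Working it through.** **Inputs from the protocol**
- Arm size: 15 in each of three groups (Table 2). Section 12.8 gives 30 active plus 15 placebo, and 30 + 15 = 3 × 15 = 45, so the two agree. The size is justified by historical practice, so there is no power calculation to reproduce.
- HAI sampling: Days 1, 29, 57, 85, 119 and 180, six titers per participant (Table 1).
- Set rule: section 12.1, as quoted above.

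**Not given, so assumed:** the seroconversion rate, the number of late deviations and the risk of one.

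**Step 1. Does the measurement flag rescue early titers?** The three conditions are joined, so all must be met. The flag only decides whether a measurement counts towards the first. A participant with valid Day 29 and Day 57 titers meets that condition but still fails the third.

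**Step 2. Titers lost per participant**

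| Deviation falls between | Titers already taken | Kept as written | Kept if only later titers are excluded |
|---|---|---|---|
| Days 57 and 85 | 3 (Days 1, 29, 57) | 0 | 3 |
| Days 85 and 119 | 4 | 0 | 4 |
| Days 119 and 180 | 5 | 0 | 5 |

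**Step 3. Share of an arm lost at Day 29.** One participant is 1/15 = 6.7%, two are 2/15 = 13.3%, three are 3/15 = 20%.

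**Step 4. Precision.** SE = √(p(1 − p)/n). At an assumed p = 0.60, p(1 − p) = 0.24.
- n = 15: √(0.24/15) = 12.6 points
- n = 14: √(0.24/14) = 13.1 points
- n = 13: √(0.24/13) = 13.6 points
- n = 12: √(0.24/12) = 14.1 points

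The relative increase does not depend on p. It is √(15/14) = 1.035 for one loss and √(15/12) = 1.118 for three, so 3.5% to 12%.

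**Step 5. How likely is at least one loss?** P = 1 − (1 − d)ⁿ, with d the assumed risk of a late deviation per participant.

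| d | One arm of 15 | All 45 |
|---|---|---|
| 2% | 26% | 60% |
| 5% | 54% | 90% |
| 10% | 79% | 99% |

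**The case against.** The best defence has four parts.

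- **The clause can be read narrowly.** It covers only deviations that affect immunogenicity data and could be applied visit by visit, with the measurement flag handling late samples. That would be sensible practice, but the sentence defines which participants belong to the set and gives no visit-level scope. The two routes need reconciling.
- **The SAP may settle it.** It commonly lists which deviations count and sets visit denominators, and no fault is found with leaving that to it. But the protocol is not silent on the unit of exclusion: it names the participant. A visit-level rule in the SAP would depart from section 12.1.
- **The example may not be a deviation.** The words "planned receipt of influenza vaccine through the duration of the study" come from an eligibility criterion, and section 6.2.1 lets the investigator permit some approved vaccines around dosing. Whether an unplanned later influenza vaccination counts is an assumption. The point concerns any late deviation judged to affect titers.
- **The effect is small.** This is accepted. The study is exploratory, its primary objective is safety, and immunogenicity is descriptive.

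A reader might go further and infer that early exits dilute seroconversion, since one pre-dose sample satisfies the entry condition. The document does not support this. It names no seroconversion denominator and does not call missing titers non-response; after withdrawal of consent, section 9.1.2 says "the data that would have been collected at subsequent visits will be considered missing". The loss would be 2.7 to 5.3 points per early exit, at assumed rates of 40% to 80%, only if the whole set were the denominator. It is zero if the denominator is those with data at the visit. Nor does someone without a post-dose titer enter a post-dose GMT or an individual fold rise.

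**Conclusion.** The point holds for the deviation clause. As written, section 12.1 lets a late deviation remove sound earlier titers, and the measurement-level flag does not restore them. Each such participant costs about 7% of an arm. One to three losses raise the standard error of a 60% rate from 12.6 to between 13.1 and 14.1 points. The 60% rate, the number of losses and the deviation risks are assumptions. The interim discrepancy also assumes that the Day 57 analysis includes HAI.

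A reader might also infer a bias in the dose comparison. Nothing in the protocol indicates that late deviations would differ by arm, so the supported conclusion is avoidable loss of data and possible inconsistency between interim and final results. It is a modest defect in secondary analyses and easily corrected.

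**What to change.** In section 12.1, and in the SAP to match:

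1. Replace the participant-level deviation condition with a sample-level one. Exclude titers collected after the deviation, or directly affected by it, and keep earlier valid titers.
2. Remove the whole participant only for a deviation at or before dosing that invalidates all of their titers.
3. For the change-based endpoints, fold rise and seroconversion, require a valid baseline and a valid titer at the visit, and use participants with both as the denominator.
4. Do not require a baseline for post-dose GMT or seroprotection. Making it a condition of set membership would discard usable post-dose titers from anyone whose Day 1 sample is lost or invalid.

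This needs a few sentences and no new data. The cost is that denominators vary slightly between visits and endpoints and must be printed in each table.

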## **6.2 Other Treatments**

### **6.2.1 Concomitant Therapy**

Concomitant therapy for intercurrent medical events should be discussed between the sponsor and the investigator or his designee.

Approved killed, inactivated, peptide, deoxyribonucleic acid and ribonucleic acid (RNA) vaccines may be permitted 30 days prior to VX-103 dosing or 60 days after VX-103 dosing according to the investigator's discretion and per local guidance. All medications, procedures, and significant non-drug therapies (including physical therapy) administered after the participant was enrolled into the study must be recorded on the appropriate electronic case report form (eCRF).

Each concomitant drug must be individually assessed against all exclusion criteria/prohibited medication. If in doubt, the investigator should contact the Sponsor's medical monitor or designee before randomizing a participant or allowing a new medication to be started. If the participant is already enrolled, contact Vaxess or designee to determine if the participant should continue participation in the study.

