### **6.4 Treatment blinding**

All groups are unblinded except the rater and subject who will remain blinded to study treatment throughout the study, except where indicated below.

The identity of the treatments will be concealed by the use of study vaccines that are all identical in packaging, labeling, schedule of administration, appearance, and odor.

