#### **Sponsor staff**

The following unblinded sponsor roles are required for this study:

- Unblinded clinical staff managing drug re-supply to site
- Blinded sample analyst(s) (immunogenicity)

The monitors are not provided with a randomization list directly but will be unblinded through review of source documentation compiled by the unblinded pharmacist or designee, which details treatment allocation to individual participants. The monitors will also be able to review the treatment allocation information/randomization list provided to the unblinded pharmacist. The name(s) of the monitor(s) are detailed in the monitoring plan, if applicable.

Sponsor or designee clinical staff are required to assist in the management and re-supply of investigational drug product. These individuals are not provided with randomization lists directly but may be unblinded through communication of drug re-supply needs via the unblinded site pharmacists.

The sample analysts will receive a copy of the randomization schedule to facilitate analysis of the samples. The sample analysts will provide the sample data to the study team under blinded conditions unless otherwise allowed.

The study statistician will be able to access the full randomization list from the start of the study and is allowed to share unblinded information with the rest of the clinical trial team as appropriate for internal decision purposes, as outlined in [Table 4](#). For example, unblinded summaries and unblinded individual data can be shared with the team whenever necessary.

Study programmers and other personnel involved in study data analysis (e.g. immunogenicity expert) are allowed to access treatment assignment information from the start of the study for the purpose of data analysis.

The Vaxess clinical trial team is allowed to share unblinded results with other sponsor staff (e.g. decision boards) as required for internal decision making on the study or the project while the study is ongoing.

All unblinded personnel will otherwise keep randomization lists and data or information that could unblind other study team members confidential and secure except as described above.

Following final database lock, all roles may be considered unblinded.

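### Immunogenicity-set exclusions rest on judgement, and the protocol does not shield that judgement from knowledge of arm and HAI titre

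*Protocol*

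**What the plan says.** **Analysis set (Section 12.1).** A participant enters the immunogenicity set if dosed, with "at least one available valid (i.e. not flagged for exclusion) immunogenicity concentration measurement", and "with no protocol deviations that impact immunogenicity data". The protocol does not say who sets a flag, who judges whether a deviation affects the data, or when either is done. The safety set, by contrast, is everyone who received study treatment.

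**Blinding (Section 6.4, Table 4).** The general rule is "All groups are unblinded except the rater and subject who will remain blinded to study treatment throughout the study". On the sponsor side, "The study statistician will be able to access the full randomization list from the start of the study", and programmers and others involved in analysis, with the immunogenicity expert as the example, "are allowed to access treatment assignment information from the start of the study for the purpose of data analysis". Individual unblinded data may be passed to the team during the study when needed. Table 4 marks all roles other than participants and rater-only staff as 'UI' at treatment allocation and dosing. Its key defines 'UI' as a permission to be unblinded at participant level.

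**Sample analysts (Section 6.4).** They are described as blinded, but within a list of unblinded sponsor roles. The same section then gives them the randomization schedule.

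**Database lock (Section 11.2).** Once the database is complete, "it will be locked, and the treatment codes will be unblinded and made available for data analysis".

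**Interim (Section 12.7).** An analysis follows completion of Day 57, while HAI sampling continues at Days 85, 119 and 180.

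**The concern.** Both exclusion criteria are applied after randomization and both need judgement. Whether a sample is invalid, or whether a deviation affected the antibody response, is often a close call. If the person making the call can see the arm and the titre, similar cases can be treated differently in different arms without anyone intending it. The HAI comparison would then no longer be protected from knowledge of outcome.

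The results at stake are the HAI geometric mean titre, fold rise and seroconversion. They support the secondary immunogenicity objective and the dose-sparing comparison of 7.5 with 15 µg. Section 8.5.1 states that fold rises will be compared across treatment groups, so these are not purely single-arm descriptions.

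**Working it through.** **Step 1. Is any deciding role required to be masked?**

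| Question | Protocol text | Answer |
|---|---|---|
| Are the exclusions judgement-based? | 12.1: flags, and deviations affecting the data | Yes |
| Is a deciding role or time stated? | 12.1 | No |
| Which roles must stay blinded to allocation? | 6.4, Table 4 | Raters and participants only |
| Could HAI titres be known before later exclusions are settled? | 12.7 interim after Day 57; samples run to Day 180 | Yes |
| When are codes available for analysis? | 6.4: from study start. 11.2: after lock | Contradictory |

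No role likely to classify samples or deviations is required to be masked. The last row is a contradiction in the text whatever a statistical analysis plan says.

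**Step 2. How much can a few exclusions move the results?** Section 12.8 gives 30 active plus 15 placebo participants, that is 45, which agrees with 3 × 15 in Table 2. It states no power, alpha or effect size, so there is no planned figure to reproduce. Everything below is illustration. The responder counts, standard deviations and 5% level are assumptions.

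*Seroconversion rate.* With x responders of 15 and k non-responders excluded, the rate becomes x/(15 − k). For x = 9:

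- k = 0: 9/15 = 60.0%
- k = 1: 9/14 = 64.3%
- k = 2: 9/13 = 69.2%
- k = 3: 9/12 = 75.0%

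For k = 2 the rise is 6.2 points if x = 6 (40.0% to 46.2%) and 12.3 points if x = 12 (80.0% to 92.3%).

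*Against an assumed 4/15 in the other arm*, the two-sided Fisher p-value is 0.139 for 9/15, 0.066 for 9/14 and 0.056 for 9/13. The protocol names no between-arm test for seroconversion; Fisher's test is used here only as a gauge.

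*Geometric mean titre.* Simulating 15 normal log2 titres and removing the k lowest multiplies the expected GMT by:

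| k | log2 SD 1.0 | log2 SD 2.5 |
|---|---|---|
| 1 | 1.09 | 1.24 |
| 2 | 1.17 | 1.49 |
| 3 | 1.26 | 1.76 |

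*False-positive rate.* Take two identical arms of 15 and a two-sided t-test at 5%, with the k lowest titres removed from one arm only. The simulated rejection rate is about 5% for k = 0, 7% for k = 1, 11% for k = 2 and 16% for k = 3.

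These are worst-direction cases: every exclusion falls on a low responder in the same arm. They show how sensitive 15 per arm is, not what is expected to happen.

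**The case against.** Several counter-arguments have weight.

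- **No decision-maker is named.** A reader might infer that unblinded sponsor staff decide the exclusions. Section 12.1 does not say so. The supported statement is that no masked decision-maker is required.
- **'UI' is a permission.** A reader might also infer that a blinded review has become impossible. That does not follow. Section 6.4 asks unblinded staff to keep allocation confidential outside the stated uses and has sample data passed on blinded unless otherwise allowed. A person who has not used the permission could still be chosen.
- **Concomitant medication.** Section 6.2.1 sends doubtful cases in enrolled participants to the sponsor, to "contact Vaxess or designee to determine if the participant should continue participation in the study". It is tempting to read this as a second way of shaping the set. It is not: one valid measurement is enough for entry, and Section 9.1.1 keeps participants in follow-up unless they withdraw consent. At most, later timepoints could be missing.
- **Detail may belong in the statistical analysis plan.** This holds for the list of excluding deviations and the review procedure, and their absence is not criticised here. The wide unblinding permission and the conflict with Section 11.2 are fixed by the protocol itself.
- **The stakes are limited.** The trial is an exploratory first-in-human study with safety primary, and HAI is secondary. Section 12.5.3 lists every participant's immunogenicity results, so an excluded titre need not be hidden. A listing is not a summary by arm, however.

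**Conclusion.** The point holds as a modest, inexpensive improvement. Exclusions that need judgement, permission for almost every role to see individual allocation, and a possible release of titres after Day 57 together leave the secondary HAI results open to selection by arm and titre. Sections 6.4 and 11.2 cannot both stand as written.

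With 15 per arm, two exclusions could shift a seroconversion rate by about 6 to 12 points and a GMT by a factor of about 1.2 to 1.5, if all fell on the lowest responders of one arm. Those sizes rest on assumed counts and SDs. The primary safety analysis is not affected, and no misconduct is implied.

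**What to change.** 1. **Section 12.1.** State that exclusion flags and deviations affecting immunogenicity are decided from a listing masked to treatment and titre, by an existing role that has accessed neither allocation nor HAI results. Sign off in two stages: data through Day 57 before the interim HAI release, and later data before the later HAI results are released. A single sign-off before the interim could not cover samples taken up to Day 180.
2. **Table 4.** Keep that one role at 'B' through treatment allocation and dosing, until its sign-off is complete.
3. **Sections 6.4 and 11.2.** Reconcile when codes become available for analysis, and settle whether the sample analysts are blinded or hold the randomization schedule.
4. **Supporting analysis.** Also summarise HAI in all dosed participants with a titre, so that the effect of exclusions is visible.

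The cost is protocol wording, one masked listing and one extra set of tables. The designated role cannot see unblinded data until its sign-off is complete. Other sponsor access can stay as it is.
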